## 11. Outcomes and Data Analysis

### 11a. Outcomes

#### 11a i. Primary outcome

Track 1: The primary outcome for Track 1 is the proportion of subjects in each group alive, in care and virally suppressed at the routine six-month on ART monitoring visit within 10 months of a positive HIV test or initial HIV care visit if previously diagnosed. The analysis period will start at study enrollment and continue through the earlier of the patient's six-month viral load or 10 months after the patient's HIV test.

Under South African treatment guidelines, all ART patients have a monitoring viral load done at six months after ART initiation. We will use this measure to assess our primary outcome. In order to create comparable follow-up time in both groups and to allow all subjects enough follow up time to have a six-month viral load, for the primary outcome analysis we will consider all ART-eligible patients who do not have a six-month viral load for any reason within 10 months of study enrollment to be failures. Viral suppression will be defined as <50 copies/ml. Patients in the rapid group who do not initiate treatment on the day of their HIV test will remain in the intervention arm for analysis (i.e. intention to treat).

Our primary outcome will be measured 10 months after study enrollment because the first 6 months on ART is the time when patients are most likely to be lost or die. At the 10-month point after study enrolment, all subjects who started ART within 3 months of enrolment will have had the opportunity for at least 6 months of exposure to treatment and allow an additional month for subjects to return to the clinic for their routine 6-month viral load test. If rapid initiation triggers a higher rate of loss to follow up after starting treatment, the impact is likely to be evident within six months of initiation. Six months of ART is also sufficient to achieve viral suppression in the vast majority of patients. In an analysis of >13,000 patients who initiated ART at a large clinic in Johannesburg, 75-80% of all patients were virally suppressed after a median (IQR) of 3.9 (3.7-5.0) months. We would thus expect at least 80% of patients to reach viral suppression by 6 months on ART.

Track 2: The primary outcome for Track 2 is the proportion of subjects in each group who adhere to ART or the prior PMTCT regimen until delivery. The number of weeks a pregnant woman is on ART before delivery is the most important predictor of perinatal HIV transmission. The guideline change to immediate ART initiation for pregnant women is likely to lead to earlier initiation for most pregnant women, but the intervention will be effective only if patients adhere to ART through the duration of pregnancy. Adherence will be measured as making monthly medication pickups to allow a continuous supply of ARVs through delivery. The analysis period for the primary outcome will start on the day of study enrollment, which is the date of a positive HIV test or the first antenatal visit of the current pregnancy, for women previously diagnosed, and end at the actual or estimated delivery date.

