## **1. Summary**

One of the most serious challenges facing antiretroviral therapy (ART) programs for HIV/AIDS in resource-constrained settings is the failure of ART-eligible patients to complete the steps required to initiate treatment. The high rate of loss to care of patients who are treatment-eligible at HIV diagnosis may be due in part to the large number of steps required between receiving an HIV diagnosis and obtaining the first dose of antiretrovirals (ARVs). In South Africa, these steps usually require approximately four clinic visits over a period of 2-8 weeks before a patient can start treatment. One strategy proposed for reducing losses among those eligible for ART is to simplify and condense the steps required for starting treatment. This is now possible because new, point-of-care (POC) tests for CD4 counts and TB diagnosis are available. These technologies can be combined with changes to clinic schedules to allow all steps required for ART initiation under South African guidelines (lab tests, physical exam, education) to take place on the day the patient presents for an HIV test.

This study is a randomized strategy evaluation of the feasibility, effectiveness, and cost-effectiveness of rapid ART initiation. Outpatient, non-pregnant, HIV-positive adults who come to a South African clinic for an HIV test, consent to study participation, and are eligible for ART will be randomized 1:1 to rapid ART initiation or to standard care. Those who are assigned to rapid ART initiation will have the possibility of receiving their first dose of ARVs as early as the same day, while those who are assigned to standard care will follow the clinic's usual procedures for starting ART. Rapid ART initiation for HIV-positive pregnant women, which has recently become the standard of care in South Africa, will also be assessed in a programmatic evaluation conducted alongside the randomized evaluation, with a retrospective comparison group. The primary study outcome for non-pregnant adults will be remaining alive, in care and virally suppressed 10 months after having a positive HIV test or CD4 count at the study site. The primary study outcome for pregnant women will be adherence to ART until delivery. The cost effectiveness of the rapid initiation strategy will be assessed as the cost per patient achieving the primary outcome for each population.

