### *6c iii. Baseline lab tests, physical exam, and educational session*

Subjects who are eligible for ART will be enrolled in the study once treatment eligibility is confirmed. Using the same blood sample drawn earlier, the study nurse will perform the required baseline blood tests (creatinine, hemoglobin, ALT) and will perform a pregnancy test for female subjects in Track 1. (Track 1 rapid group subjects who are found to be pregnant will be transferred to Track 2 at this time.)

Subjects will then be examined by the study nurse, who will conduct the standard ART readiness physical examination. Either before or after the medical exam, depending on each day's patient flow, each subject will also meet individually or in a small group with the trained study assistant for an educational and counseling session on antiretroviral therapy, the importance of adherence and disclosure, and other actions to promote health while on ART. This will be a concise version of the education and counseling typically provided over the course of three visits under standard care. During this session, each subject will have an opportunity to ask questions and discuss concerns with the study assistant.

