Medical record data for study subjects will be downloaded from the site's existing electronic medical record system, as described above. Records in this system are created only when patients initiate ART, and thus do not capture pre-ART care (HIV tests, monitoring CD4 counts, etc.). The lead data analyst will be responsible for ensuring that study identification numbers are correctly matched to the record numbers in the MRS. In instances where the data analyst cannot match a study ID number to an electronic medical record number using only the fields in the study linking file, a query will be sent to the on-site study staff, who will access the clinic's paper-based patient files to determine whether the subject ever initiated ART and, if so, locate the correct MRS number.

For subjects in the standard group, eligibility for study enrollment can only be determined once treatment eligibility is established by CD4 count or other criterion. For these subjects, the study team will review the site's paper-based patient files on a monthly basis to determine whether and when the subject has been found eligible for treatment and if treatment has been initiated. This information will be entered onto case report forms and captured in the REDCap database as described above.

A note or tab indicating that a patient is a participant in the study will be attached to the cover of each subject's paper medical record at the study site, to assist site and study staff in locating study subjects' files should this be necessary and to ensure that site staff are aware of which patients are study participants.

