## 10. Sample Size

Track 1: In a recent study we conducted in Johannesburg, we found that among patients eligible for ART, 46% initiated ART within 16 weeks of eligibility. In an analysis of data from the same Johannesburg site, we estimated that among more than 3000 patients initiated on ART in 2010 and 2011 who remained in care, 77% were virally suppressed at the routine 6-month viral load. We would thus expect approximately  $0.46 \times 0.77 = 35\%$  of those eligible to have both started treatment and be virally suppressed by the 6-month viral load. For our study site we conservatively estimate that 50% of those eligible for treatment in the standard group will be suppressed by 10 months after their HIV test. We anticipate that the rapid initiation strategy will increase the proportion suppressed to 70%.

For our primary analysis, using an  $\alpha$  of 0.05, power of 90%, 1:1 randomization, and an uncorrected Fisher's exact test, we would need to enroll 124 HIV positive ART-eligible subjects per group (248 total). We expect 70% of all HIV-positive patients to be eligible for ART under current South African guidelines on the day they test positive for HIV or make their first HIV care visit, based on results from published studies in South Africa. Therefore to reach 124 subjects per arm who are treatment eligible on the day of testing we will need to consent 177 subjects per group (354 total). To allow stratification in the analysis by sex and by site, we will consent up to 300 per group (600 total) to have adequate power. We will enroll in the study up to 67% of this total (enrollment=400).

The sample size for the Track 1 retrospective comparison group will be 120. This group will be limited to patients already found to be eligible for ART at one of the two study sites (Thuthukani). They will be compared with each of the two randomized prospective groups (rapid and standard). We expect that Thuthukani will account for approximately 60% of total prospective enrollment of 400, or 120 in each of the randomized prospective groups. We will thus aim to enroll the same the number of subjects into the retrospective comparison group as in each prospective group.

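### The Track 1 primary outcome has no single time zero, so the 10-month deadline for the six-month viral load can fall later in the standard arm

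*Protocol*

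**What the plan says.** The protocol uses several origins for the same 10-month window.

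- **Section 11a i, definition:** a positive HIV test, or the first HIV care visit for those already diagnosed.
- **Section 11a i, analysis period:** "The analysis period will start at study enrollment and continue through the earlier of" the six-month viral load or ten months from the HIV test. It opens on one clock and closes on another.
- **Section 11a i, failure rule:** ART-eligible patients who "do not have a six-month viral load for any reason within 10 months of study enrollment to be failures". The rationale that follows also counts from enrollment.
- **Section 1 (Summary):** "remaining alive, in care and virally suppressed 10 months after having a positive HIV test or CD4 count at the study site".
- **Section 4a:** an HIV test or entry into HIV care.
- **Section 10:** the control rate assumes that "50% of those eligible for treatment in the standard group will be suppressed by 10 months after their HIV test".
- **Sections 6e ii, 11a ii (item 1) and 11c:** follow-up and cost windows run from enrollment.

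Enrollment has two meanings. In section 5c it is the day of the HIV test, CD4 sample or CD4 result. Section 6b iv opens an envelope for each subject already called enrolled. Section 6d i says contact with standard subjects stops after enrollment, and section 6e i puts that point at randomization. But section 6b vi enrolls only those found eligible, after consent and randomization. Section 6c iii states that "Subjects who are eligible for ART will be enrolled in the study once treatment eligibility is confirmed". Section 8f ii says of the standard group that "eligibility for study enrollment can only be determined once treatment eligibility is established by CD4 count or other criterion". Section 6d i, in its next sentence, has laboratory results monitored to decide who should be enrolled.

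**The concern.** A missing six-month viral load counts as failure, so the closing date of the window decides outcomes. If the clock starts when eligibility is confirmed, it starts after randomization and at an event whose timing depends on arm. Section 11a i adopts the cap to give both groups comparable follow-up, and a cap can do that only if it has one origin. The same endpoint drives the interim stopping rule in section 12g.

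The HIV-test end date raises a second problem. Section 5c admits patients diagnosed earlier, for whom ten months from the test may be nearly over, or already over, at entry.

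**Working it through.** **1. The plan's own figure.** Section 10 gives 50% against 70%, "power of 90%, 1:1 randomization, and an uncorrected Fisher's exact test", alpha 0.05. Two-sided, pooled variance, no continuity correction:

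n = [1.960 × √(2 × 0.6 × 0.4) + 1.282 × √(0.5 × 0.5 + 0.7 × 0.3)]² / 0.20² = (1.358 + 0.869)² / 0.04 = 124 per group.

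This reproduces the stated 124. Nothing in this point changes it.

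**2. Deadline under each sense of enrollment.** One month is taken as 30.44 days, so 10 months is 304 days and 6 months is 183 days. The latest ART start that still allows a six-month viral load is 4 months, or day 122, after the origin.

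- Enrollment is the randomization day: the deadline is day 304 in both arms.
- Enrollment is eligibility confirmation: day 304 for a rapid subject confirmed the same day. For a standard subject awaiting a CD4 result it is day 304 + 7 = 311, using the lag of about one week in sections 6b vi and 6d i. The latest ART start becomes day 129.

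Example: two newly tested subjects, one per arm, both start ART on day 125. Their viral loads fall due on day 125 + 183 = 308. The rapid subject has missed day 304 and fails. The standard subject is inside day 311 and can succeed.

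**3. Size of a 7-day lag (illustration).** Assume ART starts at a constant hazard, with 46% started by 16 weeks (112 days) and 77% of starters suppressed, both from section 10.

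- h = −ln(1 − 0.46) / 112 = 0.00550 per day
- Started by day 121.75: 1 − exp(−0.670) = 48.8%
- Started by day 128.75: 1 − exp(−0.708) = 50.7%
- Extra successes: 0.019 × 0.77 = 1.5 points

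Raising the 16-week figure to 65% (about 0.50 / 0.77, to match the planned 50%) gives 1.6 points. The standard rate would move from 50% to between 51% and 52%. Power against 70% would then lie between 87% and 83% at 124 per group, and between 97.5% and 96% at the 200 per group implied by enrolling 400.

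**4. The HIV-test end date.** A six-month viral load within 10 months of the test requires ART within 10 − 6 = 4 months of the test. For a subject tested 6 months before entry, the period closes 4 months after entry, so success is impossible even with same-day ART. For one tested 10 months before entry, the period closes on the day it opens.

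**The case against.** Several parts of the case on the other side stand.

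- **Enrollment may simply mean the visit day.** Sections 5c, 6b iv and 6e i support that, and day 0 is then the same in both arms for newly tested patients. An arm-dependent origin is one of two readings, not an established fact. Subjects arriving with a qualifying CD4 result have no lag on either reading.
- **The HIV-test clause may be shorthand.** The sentence before it gives previously diagnosed patients a care-visit anchor, and the failure rule runs from enrollment. That is probably the intent, but the text does not say so.
- **A reader might infer a lag of a month or more from the monthly file review.** Section 8f ii has that review establish whether and when eligibility was found, so it need only recover a date, and section 8e already collects eligibility dates. A 37-day lag would add about 7 points (57% against 70%: power 57% at 124 per group, 77% at 200). It requires assuming that the review date becomes the enrollment date, which the protocol does not state.
- **A reader might also infer that stopping at the six-month viral load is an error.** It falls near month 6.0 for a same-day starter and month 7.4 at the 42-day mean quoted in section 3b, so retention is judged at different times since randomization. But section 11a i defines the outcome at the six-month on-ART visit and gives a reason: excess loss should show within six months of starting. Section 4a also says within 10 months. Later retention is covered by secondary outcome 3 and by follow-up of up to 24 months. This is a reasoned choice; only the Summary's wording conflicts with it.

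**Conclusion.** The point holds as a contradiction in the definition of the primary outcome. The deadline that turns a missing viral load into a failure has no single origin, and on one of two readings it differs by arm. The documented lag supports about 7 days for standard subjects awaiting a CD4 result. That is about 1.5 points of standard-arm success, which rests on the constant-hazard assumption and on the lag applying to the whole arm. The direction is against rapid initiation. Against a planned 20-point difference this is small, but it is avoidable and sits in the primary endpoint. The literal HIV-test end date has a larger effect on those it touches, but the protocol does not say how many were tested more than 4 months before starting ART. The documents do not support a claim that time zero certainly differs by arm, or that the six-month viral load endpoint must be replaced.

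**What to change.** Define day 0 for Track 1 as the date of randomization in both arms and close the window 10 months later. In section 11a i, replace the end date counted from the HIV test with one counted from randomization, and apply the failure rule from the same date. Use that anchor in sections 1, 4a, 6e ii, 10, 11a and 11c. Give enrollment one meaning throughout, and use a separate term for confirmation of eligibility.

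Keep the six-month on-ART viral load within that window as the primary measure, and reword the Summary to say within 10 months. Being alive and in care at month 10 can be added as a secondary or sensitivity outcome from the clinic status and pickup data already abstracted.

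The cost is wording only. Randomization takes place at the consent visit, so its date is available. One item remains: the retrospective group in section 6f runs from the date eligibility was determined and cannot use randomization, so the protocol should state its nearest equivalent and acknowledge the difference.

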#### *11a ii. Secondary outcomes*

Secondary outcomes will include:

1. Average cost per patient who is alive, in care, and virally suppressed within 10 months of study enrollment (Track 1).
2. Cost per patient adhering to ART through delivery and the cost per infant infection avoided, using estimated vertical transmission rates (Track 2).
3. Proportion of subjects in each track and group alive, on ART, and virally suppressed at six-month intervals and the final date of data censoring.
4. Average time to ART initiation (days) for each track and group.
5. For Track 2, average gestational age at ART initiation (weeks) and average duration (weeks) on ART prior to delivery.
6. For Track 2, if enrollment numbers allow, proportion of subjects with CD4 count > 350 and ≤ 350 achieving the primary outcome of retention on ART (or PMTCT regimen) until delivery.
7. Patient-level predictors of treatment uptake, retention in care, and viral suppression.
8. Prevalence of TB symptoms and confirmed TB, time to initiation of TB treatment, and time to initiation of ART among patients with TB.
9. Process indicators including:
  - Acceptance of rapid initiation strategy (% of patients offered rapid initiation who accept)
  - Average time elapsed (days) between HIV test and dispensing of first dose of ARVs
  - Average cost to patients of initiating treatment, including travel and other out-of-pocket costs and time spent in clinic

All outcomes will be estimated for each study population and compared between the two study populations where relevant.

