##### 4b. Secondary objectives

1. For non-pregnant adults, compare the cost per patient alive, in care, and virally suppressed within 10 months of an HIV test or enrollment in HIV care for those offered rapid ART initiation to the cost for those offered standard care.
2. For pregnant women, estimate the cost per patient adhering to ART through delivery and the cost per infant infection avoided, using estimated vertical transmission rates.
3. Estimate the proportion of patients alive, on ART, and virally suppressed at 6 month intervals after treatment initiation and at the final date of data censoring.
4. Estimate the average time interval between HIV test or first HIV or ANC care visit and treatment or PMTCT initiation before and after rapid ART initiation became the guideline procedure for pregnant women.
5. If enrollment numbers allow, among pregnant women, stratify the primary outcome (the proportions of subjects achieving retention on ART or PMTCT regimen until delivery) by CD4 count > 350 and  $\leq 350$ .
6. Compare the average gestational age at ART initiation and average number of weeks on ART prior to delivery for pregnant women before and after rapid ART initiation became available.
7. Identify patient-level predictors of treatment uptake, retention in care, and viral suppression.
8. Describe the prevalence of TB symptoms and confirmed TB, time to initiation of TB treatment, and time to initiation of ART among patients with TB.
9. Evaluate the feasibility of the rapid initiation strategy in terms of patient acceptance, actual time between HIV test/enrollment in care and dispensing of first dose of ARVs, and patient costs incurred.

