In Track 1, those in the rapid initiation group will be offered a rapid CD4 count, rapid TB test if needed, and other rapid tests and same-day physical exam, counseling, and adherence education on the same day as study enrollment, allowing immediate ART initiation if eligible. Those in the standard group will follow the standard-of-care visit schedule and procedures, which also include a CD4 count, TB test if needed, other tests, physical exam, counseling, and adherence education, though not on a rapid schedule. Subjects in Track 1 will be prospectively followed for a minimum of 10 months. Follow-up (after treatment initiation) will be passive and by medical record review only, to prevent biasing outcomes through active follow-up and maximize the extent to which study results reflect what could be expected in a routine implementation setting. An additional retrospective comparison group for Track 1 will be enrolled comprised of patients who became eligible for ART at one of the two study sites prior to the launch of the study.

Track 2 will be an observational evaluation only. Data from before the guideline change will be collected retrospectively, from existing registers and records at the site. Data from after the guideline change will be collected prospectively from questionnaires and newly-acrued medical record data. The study will not provide any direct clinical interventions for Track 2.

Unit cost data will be collected for all resources used for patient care for both study tracks, including all drugs, diagnostics, clinical staff time, and infrastructure and other fixed costs. Quantities of resources used will be collected from study case report forms at the end of the follow up period. An average cost per patient and cost per outcome will then be calculated and compared between the strategies.

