#### *6e ii. Medical record follow up*

Study subjects will be followed through review of routine medical records kept by the study site for a minimum of 10 months after the date of enrollment in the study for Track 1. This will allow all subjects who initiate ART within 3 months of study enrollment to reach the point at which the routine 6-month viral load is called for, with an additional month allowed for the viral load test to be completed. Subjects will continue to be followed until the final date of study data censoring, up to a maximum of 24 months after study enrollment.

In the study team's experience at other clinics in South Africa, a few patients who remain in care and make a clinic visit at the point at which the routine 6-month viral load test should be done do not have viral load results reported in their medical records. Should this happen, the subject's paper file and laboratory records at the site will be reviewed to confirm that no viral load test was done. If no test was done, a note will be placed in the subject's clinic file to remind clinic staff to ask the subject to provide a sample for viral load testing when she or he next comes to the clinic for routine medication pickup, which typically takes place every 2-3 months.

A blank consent form addendum will be placed in each Track 1 subject's clinic file to be used if the subject's care is being transferred to another clinic. The addendum will request consent to collect medical record data during the follow up period from the new clinic. It will be administered by study staff only if a transfer is being processed.

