#### 7d. Record review

Study subjects will be followed through review of routine medical records kept by the study site for a minimum of the remaining months of pregnancy prior to delivery. Subjects will continue to be followed in the medical records after delivery until the final date of study data censoring, up to a maximum of 24 months after study enrollment.

Delivery information (date and outcome of delivery) that is not found in the study site's own records will be sought at one of the maternity ward facilities to which women are regularly referred for delivery, Tembisa Hospital and Esangweni Clinic. A letter indicating the approval of these facilities for this limited data collection will be submitted to the IRB prior to data collection. At these facilities, the delivery ward register and/or patient files will be used to fill in missing fields in study subject records. No additional data fields beyond what are already included in the consent forms and CRFs will be collected from these facilities. This procedure is necessary to address the problem of information that is supposed to be recorded in the study clinic files but is missing due to incomplete communications between the study clinic and delivery facilities.

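### Track 2 groups are compared at the final data-censoring date, when the pre-guideline group will usually have been followed longer than the post-guideline group

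*Protocol*

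**What the plan says.** Secondary outcome 3 (Protocol 11a ii) is the "Proportion of subjects in each track and group alive, on ART, and virally suppressed at six-month intervals and the final date of data censoring". The matching objective (4b, item 3) is worded as an estimate of the proportion alive, on ART and "virally suppressed at 6 month intervals after treatment initiation and at the final date of data censoring". So the six-month points count from the start of treatment, while the last point is a study date.

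Section 11b uses one analytic approach for both tracks and for primary and secondary clinical outcomes. Proportions for each dichotomous outcome are compared by group with crude risk ratios and 95% confidence intervals, followed by log-linear adjustment for baseline covariates.

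Follow-up to the final date differs by group:

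- **Track 2, both groups.** The analysis period for the primary outcome is set to "start on the day of study enrollment, which is the date of a positive HIV test or the first antenatal visit of the current pregnancy" (11a i). Record review covers a "minimum of the remaining months of pregnancy prior to delivery" and then runs "until the final date of study data censoring, up to a maximum of 24 months after study enrollment" (7d). The pre group comes from records before the April 2013 guideline change. The post group is enrolled prospectively after it (5a, 7, 7b).
- **Track 1, randomized groups.** "Subjects in Track 1 will be prospectively followed for a minimum of 10 months" (5a), continuing "up to a maximum of 24 months after study enrollment" (6e ii).
- **Track 1, retrospective group.** A fixed 10 months from the date of ART eligibility (6f). Section 10 says it will be compared with each randomized group.

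**The concern.** The proportion still alive and on ART falls as time since entry grows. If two groups are assessed on one calendar date and one entered care earlier, the earlier group has had longer to lose patients. A crude risk ratio then shows a difference even when retention at any given time since entry is the same. Adjusting for baseline covariates does not help, because the imbalance lies in follow-up time.

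Track 2 has this structure: the pre group entered first by definition. The 24-month cap limits the imbalance but removes it only if every post-group woman also reaches 24 months, and the stated minimum is only until delivery. At stake is a before/after comparison of a national policy on a longer-term outcome.

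The protocol applies the principle elsewhere. Section 11a i sets the Track 1 primary outcome so that follow-up is comparable between groups, and 6f fixes the Track 1 retrospective group at 10 months to match that outcome. The final-date part of secondary outcome 3 has no such protection.

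**Working it through.** The protocol gives no figure for this time point, so there is nothing to reproduce. The check asks what difference appears when retention is identical in both groups.

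**From the protocol:** cap of 24 months; pre group enters before post group; one final censoring date; about 120 pregnant women starting ART a year at the site (5b).

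**Assumed, because not stated:** uniform entry; post-group accrual A = 9, 12 or 18 months; pre group from the 12 months immediately before; censoring T months after the last post-group entry; annual attrition a, the same in both groups.

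**Formulas.** With entry time e counted from the first post-group entry, follow-up = min(24, A + T − e). Here e runs from 0 to A for the post group and from −12 to 0 for the pre group. Retention at t months is exp(−ht), with h = −ln(1 − a)/12, averaged over e.

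**Worked case: A = 12, T = 10, a = 20%.** h = 0.018595.

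- Post group: follow-up is uniform on 10 to 22 months. Mean retention = (0.8303 − 0.6643)/(12 × 0.018595) = 0.744.
- Pre group: 2/12 of women lie between 22 and 24 months and 10/12 are at the cap, where retention is 0.64. Mean = [(0.6643 − 0.6400)/0.018595 + 10 × 0.64]/12 = 0.642.
- Difference: 0.744 − 0.642 = 0.102, or 10 points, with no true effect.

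**Range over A = 9 to 18 months (post minus pre, percentage points):**

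| Last post-group woman followed | a = 10% | a = 20% | a = 30% |
|---|---|---|---|
| 10 months | 4 to 6 | 7 to 11 | 9 to 15 |
| 18 months | 0.7 to 1.4 | 1.2 to 2.5 | 1.5 to 3.1 |
| 24 months | 0 | 0 | 0 |

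With 10 months for the last woman, mean follow-up is 23 to 24 months (pre) against 14.5 to 18.6 months (post).

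**Very short post-group follow-up.** Take T = 4 and A = 15 (about 152 women at 120 a year: 152/120 × 12 = 15.2 months), with a pre group entering over 15 months and ending 1 month before the first post-group entry. At a = 20%, retention is 81.0% (post) against 64.7% (pre), a gap of 16 points. But the outcome also requires viral suppression, and 6e i places the routine viral load for adult ART patients at month 6. If post-group women with under 6 months of follow-up count as unsuppressed, 68.9% compares with 64.7%, a gap of 4 points. With a 7-month threshold it is 63.0% against 64.7%, about −2 points. Every pre-group woman has at least 4 + 15 + 1 = 20 months, so that group is unaffected.

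**Track 1 retrospective group.** At a = 20%, retention at a fixed 10 months is 83.0%. Averaged over follow-up spread evenly from 10 to 24 months it is 73.1%. Final-date status would therefore differ by 10 points between the retrospective and randomized groups with no true difference.

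**After the fix.** At one fixed time from entry, identical retention gives a difference of 0 and a risk ratio of 1.00.

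**The case against.** Objective 3 says estimate, where objectives 1 and 6 say compare, and 11a ii limits comparisons between study populations to where they are relevant. On that reading the final-date figure is already descriptive. This does not settle it: 11b explicitly compares each dichotomous outcome by group and extends that to secondary outcomes in both tracks.

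The size is uncertain, and that stands. The accrual period, the Track 2 pre-group window and the censoring date are all unstated. The 10-month tail in the first row of the table is the Track 1 minimum, not a Track 2 rule. A late enough cut-off makes the problem negligible, but nothing in the protocol requires one. Identical attrition is also a simplification: 11b notes that part of the pre group was offered AZT rather than full ART, so being on ART and suppressed after delivery would differ by regimen anyway.

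Three stronger readings are tempting, and the document does not support them:

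- A reader might infer that the bias always favours immediate initiation. The model covers retention only. Where post-group follow-up is too short for a 6-month viral load, the error can shrink or change sign.
- A reader might extend the point to rapid versus standard in Track 1. Those arms are randomized 1:1 and enrolled concurrently, so their follow-up should be balanced. A proportion averaged over 10 to 24 months is harder to interpret but not biased between arms.
- A reader might object to the six-month points because guaranteed follow-up is only 10 months. They are anchored to treatment initiation, so the calendar-date problem does not arise. The denominator for subjects who cannot reach a later point belongs in the SAP. The rule that a missing viral load is a failure is stated for the primary outcome only.

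**Conclusion.** The concern holds for one part of secondary outcome 3: the Track 2 pre/post comparison at the final censoring date. As written, the two groups have unequal follow-up unless all post-group women reach the 24-month cap, and the planned analysis does not account for it.

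Under the stated assumptions and 20% annual attrition, the artefact ranges from zero to about 11 points as the last woman's follow-up falls from 24 to 10 months. Its direction is not fixed once follow-up is shorter than the time needed for a viral load. The same mismatch applies if the Track 1 retrospective group is compared with the randomized groups on final-date status.

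The primary outcomes of both tracks, the sample size, the interim rule and the randomized contrast are untouched. This is a correction worth making to one time point of a secondary outcome.

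**What to change.** In 11a ii and 11b, state that the Track 2 groups, and the Track 1 retrospective group against the randomized groups, are not compared at the final censoring date. Instead, use either of these:

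- Compare at fixed times from enrollment or ART start, with both groups truncated at the same follow-up length. The denominator is everyone whose entry date allows that time point before the cut-off, chosen by date and never by outcome.
- Use a time-to-attrition estimate censored at the cut-off.

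Report final-date status descriptively for each group, with the distribution of follow-up beside it. Objective 3 in 4b can keep its wording, since it asks only for an estimate.

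The change is to wording, and no new data are needed. The cost is that later time points rest on fewer subjects.
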